Prior to the enrollment of providers and patients, the NOCTEM team and the EFs and IFs will first complete an in-depth review of written guidelines and standard operating procedures for this project. During the trial, the EF and IF teams will meet monthly by phone and communicate via email, as needed, between scheduled monthly meetings to address any issues that arise and share newly acquired information. The EF and IF guidelines will be updated as needed to make sure both processes are documented and kept up to date during the trial.

The sleep intervention is the same for all patients enrolled by participating clinicians. When a disordered sleep pattern is detected by the NOCTEM algorithms (usually within 7 days), the provider will receive automated sleep recommendations for each patient and will be asked to review and confirm prior to forwarding it to the patient. Recommendations are consistent with stimulus control, sleep restriction, and other EB-BSM techniques, including suggested times for rise time and bedtime and exercise to minimize nightmares. Providers may elect to modify the algorithm-driven recommendations as they see fit, based on knowledge of their patients. Patients will receive their provider-approved, personalized behavioral sleep recommendations on a weekly basis. This process will be repeated for the next 4 to 6 weeks.

Participating patients will not be terminated from the study until (1) they decide to stop using the app; or (2) their provider deems that a different treatment or referral is required; or (3) the treatment course is complete, and the use of the app is no longer necessary; or (4) the end of the project. COAST is not commercially available, and patients who wish to remain in sleep treatment will be encouraged to discuss options with their provider. Because the COAST system requires that a provider monitors entries and sleep status and progress, the app will be disabled when a patient is no longer in the care of a provider. This will avoid misleading patients that they are still under the care of the provider through the app only.

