The second hypothesis is that COAST+EF and COAST+EF/IF will yield greater improvements in patient insomnia symptom severity than COAST only over the acute 6-week intervention period. We will compute the change in ISI from baseline to 6 weeks (∆ISI = baseline ISI − 6-week ISI), with higher ∆ISI values indicating a greater improvement over time. We will use a mixed effects model to regress ∆ISI on group, accounting for nesting within providers through a random effect and including relevant covariates. We will extract estimates from the model to compute the standardized mean difference *d* [70, 71] and 95% confidence interval between COAST and COAST+ (EF; EF/IF) accounting for patients nested within providers. Second, using a mixed effects model with a random clinician effect, we will regress ISI at baseline and 6 weeks of treatment (COAST versus COAST+EF and COAST+EF/IF), time, and their interaction, controlling for relevant covariates. A significant treatment-by-time effect will indicate that the change in ISI differs between COAST and COAST+EF and COAST+EF/IF. Assuming an average of 12 providers per group (8 in COAST and 16 in COAST+EF and COAST+EF/IF) and 36 patients per clinician, we expect 0.80 power (alpha = 0.05) to detect a standardized mean difference of 0.232 between groups. We will also evaluate the extent to which COAST+EF is not inferior to COAST+EF/IF as measured by changes on the ISI over the acute 6-week intervention period. This non-inferiority hypothesis will be tested with the general form—H_0_: COAST+EF is inferior to COAST+EF/IF versus H_1_: COAST+EF is non-inferior to COAST+EF/IF. Using the methods described above, we will compute the standardized mean difference *d* and 95% confidence interval [*d* (95% CI)] for COAST+EF − COAST+EF/IF of ∆ISI. As positive values of ∆ISI indicate more improvement, a positive *d* is in favor of COAST+EF and a negative *d* is in favor of COAST+EF/IF. We will use a non-inferiority margin (NIM) of − 0.50 and declare COAST+EF to be non-inferior to COAST+EF/IF if the lower bound of the 95% CI for *d* is > − 0.50. We will declare COAST+EF to be inferior to COAST+EF/IF if the lower bound of the 95% CI for *d* is ≤ − 0.50. For example, if *d* (95% CI) = − 0.10 (− 0.40, 0.20), we would declare COAST+EF as non-inferior to COAST+EF/IF because − 0.40 > − 0.50. However, if *d* (95%CI) = − 0.40 (− 0.70, − 0.10), we will declare COAST+EF to be inferior because − 0.70 ≤ − 0.50. These one-sided decision rules equate to requiring the effect size of the COAST+EF to COAST+EF/IF comparison to have no more than moderate strength (|d| = 0. 5), in favor of COAST+EF/IF. The NIM of |d| = 0.5 set to determine non-inferiority is stringent as it represents 50% of the effect size reported in recent meta-analyses [50, 72, 73]. Assuming 8 providers per group and 36 patients per clinician, an intra-class correlation of 0.01 [74], a non-inferiority margin of 0.50, and a true difference of δ = 0, we expect > 0.99 power to reject our null hypothesis and conclude that COAST+EF is non-inferior to COAST+IF/EF.

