
## Secondary and exploratory analyses

Secondary analyses will explore the durability of symptom improvements over time among patients who used the COAST platform with their provider over time. While the time elapsed between the post-treatment at 6 weeks and discharge may vary across patients, we will, nevertheless, explore the extent to which detectable sleep improvements after 6 weeks may persist over time. The variability in elapsed time between the post-treatment and discharge assessment will be taken into consideration in the statistical analyses. We will first summarize and compare the differences in discharge times by examining relevant baseline characteristics (e.g., symptom severity, sleepiness, daytime impairments). We will then compute the average rate of change in ISI score per month [(6-week ISI − discharge ISI)/(discharge week − 6)]. Using a mixed model, we will fit an intercept-only model for the rate of change in ISI score, accounting for nesting within clinician through a random effect. An intercept that differs significantly from zero will indicate further change in ISI score between 6 weeks and discharge. Models will also include age and sex and other baseline characteristics that may be found to impact time to discharge. Finally, we will explore whether change in psychological distress (e.g., PHQ-8, GAD-7, PCL-5) corresponds to use of COAST by computing correlations between change in ISI score, and number of interactions with their assigned coach.

While the study is not powered for definitive determination of the effects of each of the clinician characteristics on implementation measures or patient outcome data, we will complete exploratory analyses to evaluate if these variables may impact outcomes of interest to inform future implementation efforts.

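### The exploratory contact-and-benefit analysis correlates ISI change with a raw interaction count, so it can reflect length of stay on the app, in either direction, rather than contact

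*Protocol article*

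**What the plan says.** The last analysis described under Secondary and exploratory analyses has this aim: "we will explore whether change in psychological distress (e.g., PHQ-8, GAD-7, PCL-5) corresponds to use of COAST". The method is "computing correlations between change in ISI score, and number of interactions with their assigned coach". So both the measure of use (a plain number) and the method (a correlation) are stated. The sentence does not say over what period interactions are counted.

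Elsewhere the article shows that time on the app differs between patients:

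- Intervention, on weekly recommendations: "This process will be repeated for the next 4 to 6 weeks".
- Intervention, on leaving. A patient may stop using the app, be moved to another treatment or referral, reach the end of the project, or finish because "the treatment course is complete, and the use of the app is no longer necessary". In addition, "the app will be disabled when a patient is no longer in the care of a provider".
- Secondary and exploratory analyses: "the time elapsed between the post-treatment at 6 weeks and discharge may vary across patients".

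The only change in ISI that the article defines by name has a fixed window (Statistical analyses plan and power calculations): "We will compute the change in ISI from baseline to 6 weeks".

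**The concern.** Interactions can accrue only while the app is active. A raw count is therefore roughly contact rate multiplied by time on the app. If time on the app is related to response, the count is related to response even when contact does nothing.

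The same section handles elapsed time elsewhere. The durability analysis divides the ISI change by the time since week 6 and includes a random clinician effect. The statement that variable elapsed time will be considered refers to the interval from post-treatment to discharge, and nothing ties it to the interaction count. The correlation also ignores clinician, although patients are nested in providers and the Discussion reports that a pilot found providers differed widely in taking up the technology.

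This is the only stated patient-level analysis that sets amount of contact against symptom change. What is at stake is whether its result can be read as saying anything about contact.

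**Working it through.** The documents give no expected correlation, power or sample size for this analysis, so there is no figure of the plan's to reproduce.

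**1. Does exposure vary?** Yes. The planned course alone runs from 4 to 6 weeks, a ratio of 6/4 = 1.5. Early stopping, referral and variable discharge widen this by an amount the article does not give.

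**2. Is exposure related to response?** The documents do not say. Finishing because the app is no longer needed could take good responders off sooner. Stopping, or being referred elsewhere, could take poor responders off sooner. The two act in opposite directions on the correlation.

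**3. How large could the artefact be?** An illustration: 400 replicates of 864 patients (the minimum patient sample). Improvement Y is standard normal and contact has no effect. The count is Poisson with mean 1 x T, where T is weeks on the app. Every patient contributes an improvement score. All inputs except 864 are assumptions. The parameter ρ sets how strongly exit depends on response, and e is independent standard normal noise.

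- (a) T = 6 for everyone.
- (b) Slower improvers stay longer: T = 2 + 6·exp(0.4u), with u = -ρY + √(1-ρ²)·e.
- (c) Poor responders leave early: the lowest quarter of u = ρY + √(1-ρ²)·e leave at a time uniform between weeks 1 and 4; the rest stay 6 weeks.
- (d) Both: early leavers as in (c), the rest as in (b).

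Mean correlation of improvement with the raw count:

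| Exit pattern | ρ = 0.2 | ρ = 0.4 | ρ = 0.6 |
|---|---|---|---|
| (a) same 6 weeks | 0.00 | 0.00 | 0.00 |
| (b) slower improvers stay | -0.13 | -0.26 | -0.39 |
| (c) poor responders leave early | +0.09 | +0.16 | +0.24 |
| (d) both | 0.00 | +0.01 | +0.04 |

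For scale, the correlation detectable with 80% power at two-sided 0.05, ignoring clustering, is tanh[(1.960 + 0.842)/√(864 - 3)] = tanh(0.0955) = 0.095. Most of the values in rows (b) and (c) exceed that.

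A second set of assumptions gives the same picture for the first mechanism. ISI change has mean 7 and SD 5; stay is 6 weeks plus an exponential tail of mean 4, shortened by 0, 0.1, 0.25 or 0.5 week per extra ISI point and held between 4 and 24 weeks; there are 1.5 contacts per week. Mean correlations are 0.00, -0.11, -0.26 and -0.45. This model allows no exit before week 4 and no early loss of poor responders, so its negative sign is built in.

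**4. What do the remedies remove?** Dividing by weeks on the app brings the correlation to about 0.00 in all of (a) to (d). A count limited to weeks 0 to 6 removes what accrues after week 6, but not early exit: in (c) every stay is 6 weeks or less, so the limited count equals the raw count. Active weeks therefore need to be shown beside it.

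Neither remedy deals with need. The Background says providers may see complex patients more often or for longer. If the weekly contact rate is multiplied by exp(-0.2Y), so that it falls as improvement rises, the correlation is -0.44 even in (a). The per-week rate stays between about -0.37 and -0.50 in (b) to (d).

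**The case against.** The strongest reply is that this is a condensed article and the sentence is silent on the window rather than wrong about it. The one ISI change defined by name runs from baseline to week 6. If interactions are counted over the same period, only exit before week 6 can distort the count, and most of the problem goes. That stands as a reason for a low grade. It does not dispose of the point: the article does state a plain count and a plain correlation, and the sentence directly follows an analysis that runs to discharge, so the 6-week reading cannot be assumed.

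A reader might infer something stronger: that patients stay longer because they improve less, so the analysis will show a false negative link between COAST use and benefit. The documents do not support this. No section says stay depends on response in that direction, two of the listed exit routes can push the other way, and with both mechanisms in play the artefact was near zero. A reader might also infer that the count runs to discharge; that is not stated either.

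It is also fair to say that no hypothesis or decision rule rests on this analysis. The article's figures on clinician time come from earlier work, not from this correlation.

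**Conclusion.** The point holds as a minor one. As written, the exploratory correlation uses a raw count with no window, no exposure denominator and no clinician term, while time on the app varies and may depend on response. A result of either sign could reflect length of stay rather than contact.

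The direction and size cannot be stated from the documents. The simulated range of -0.39 to +0.24 shows what assumed exit patterns could do and is not an estimate for this trial. If both variables were confined to the same 6 weeks and few patients left early, the artefact would be small. Confounding by patient need would remain under any version of the count.

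**What to change.** - State that interactions are counted from app activation to the 6-week ISI, the same window as the symptom change, and report each patient's active weeks in that window alongside, so that early exit is visible.
- Replace the plain correlation with a regression of the symptom change on this count, in the mixed model with a random clinician effect already used for the other ISI analyses.
- Name the symptom score. The sentence announces change in psychological distress and then correlates change in ISI.
- Describe the result as an association still open to confounding by patient need, which neither the common window nor a per-week rate removes.

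The cost is a few lines in the analysis plan and slightly more programming. The sustainability analysis already needs interactions placed in time, so the dates should be available. The downside is that contacts after week 6 are not used.

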## Plan for dissemination of the results

We anticipate publishing the findings of the trial in at least one peer-reviewed publication and presenting primary and secondary data analyses at national scientific conferences, including the SLEEP meeting, the Military Healthcare System Research Symposium, and the American Telemedicine Association. Briefs delivered to Navy Medical leadership will also offer a path for dissemination of the study findings. Results of the trial will also be discussed with stakeholders and leadership in the DHA.

## Discussion

This implementation-effectiveness hybrid type 3 trial is innovative in its combination of digital technologies and evidence-based CBTI practices using a pragmatic approach and a primary focus on ecological clinical validity. This trial design was selected because it is uniquely suited to identify and guide future implementation and dissemination efforts to increase uptake of EB-BSM and improve sustainable access to care and to assess patient-centered outcomes. If successful, the utilization of a dHealth platform to support CBTI can have significant benefits such as improving the overall health, readiness, and resilience of the US Armed Forces; decreasing reliance on hypnotics; improving military retention rates; and decreasing insomnia-related healthcare costs. Scalable and cost-effective digital sleep solutions can have substantial benefits for the Veterans Health Administration as well as civilian healthcare providers and payors.

Based on our preliminary findings and other large-scale research and clinical efforts in the VA and [75, 76], we expect that reach, adoption, and sustainability (maintenance) will be enhanced through EF and EF/IF. We also expect that the magnitude of improvements in insomnia achieved through delivery of CBTI via the dHealth platform for patients enrolled in the trial will meet stringent criteria for clinical effectiveness. Overall, we expect that COAST implemented in MTFs, affiliated clinics, and wellness centers will be an acceptable and preferred care delivery model for delivering behavioral sleep interventions to ADSMs with insomnia and other behavioral sleep disorders.

There are, of course, some challenges that are anticipated over the course of the study. Changes in clinic leadership may impact the retention of enrolled clinics over the course of the trial. To mitigate this risk, we will work closely with each clinic’s leadership and stakeholders to solidify and maintain engagement. Similarly, the retention of providers may be challenging, as attrition naturally occurs due to relocations, promotions, leaves, or other factors. If a clinician withdraws from the trial, we will recruit, train, and replace them with a new provider to maintain a minimum of 24 enrolled providers. A prior implementation pilot revealed high variability among providers in adopting technology. To optimize proficiency and confidence with digital technology, we will closely supervise newly trained providers during the 10- to 14-day familiarization period to provide timely, personalized feedback, and to promote engagement.

While this trial will be conducted in MTFs and affiliated clinics and wellness centers, there is high translation potential to VA Medical Centers and Community-Based Outpatient Clinics as well as to civilian healthcare settings. In civilians, insomnia affects as many as 30% of the general population [3, 77]. In both veterans and civilians, insomnia is also associated with poor mental and physical health outcomes, absenteeism, heightened risk of accidents, decreased productivity, and increased healthcare costs and utilization [15, 78–84]. The same challenges of CBTI scalability, access, and delivery are found in VA and civilian healthcare sectors, and both have called for greater use of dHealth technologies to support high-quality care and reduce rapidly growing healthcare costs.

## Data Availability

Data sharing not applicable to this article as no datasets were generated or analyzed during the current study.
